# Study protocol for a pilot randomized controlled trial on a smartphone application-based intervention for subthreshold depression

**DOI:** 10.1097/MD.0000000000018934

**Published:** 2020-01-24

**Keywords:** depression, eHealth, mHealth, mobile applications, smartphone, subthreshold depression

## Abstract

**Introduction::**

Interventions aimed at addressing subthreshold depression (StD) are important to prevent the onset of major depressive disorder. Our video playback application (SPSRS) is designed to reduce depressive symptoms by presenting positive words in videos, shedding new light on the treatment of StD. However, no randomized controlled trial (RCT) has utilized this video playback application for the treatment of individuals with StD. Therefore, a pilot RCT was designed to determine the feasibility of a full-scale trial. We herein present a study protocol for investigating the utility of a video playback application intervention for individuals with StD.

**Methods::**

This 5-week, single-blind, 2-arm, parallel-group, pilot RCT will determine the effectiveness of the video playback application by comparing individuals who had and had not been exposed to the same. A total of 32 individuals with StD will be randomly assigned to the experimental or control group at a 1:1 ratio. The experimental group will receive a 10-minute intervention containing the video playback application per day, whereas the control group will receive no intervention. The primary outcome will include changes in the Center for Epidemiologic Studies Depression Scale score after the 5-week intervention, while secondary outcomes will include changes in the Kessler Screening Scale for psychological distress and the generalized anxiety disorder 7-item scale score after the 5-week intervention. Statistical analysis using linear mixed models with the restricted maximum likelihood estimation method will then be performed.

**Discussion::**

This pilot RCT will have been the first to explore the utility of SPSRS application interventions that display positive words in videos for individuals with StD. The results of this pilot trial are expected to help in the design and implementation of a full-scale RCT that investigates the effects of SPSRS applications among individuals with StD.

**Trial registration::**

ClinicalTrials.gov Identifier: NCT04136041

## Introduction

1

Subthreshold depression (StD) has been characterized as the presence of clinically significant depressive symptoms that do not satisfy the criteria for major depressive disorder (MDD).^[1]^ Previous studies have shown that StD has a prevalence rate of 4.0% to 38.7%,^[2–4]^ which is higher than that for MDD.^[5,6]^ Despite being a precursor to MDD,^[7]^ StD has been associated with poor quality of life,^[1,7,8]^ poor health,^[9]^ impaired daily activities,^[2,10]^ considerable economic burden,^[11]^ and mortality.^[12]^ Of particular importance, StD has been considered an significant risk factor for developing MDD given that many individuals with StD develop sustained depressive symptoms and are expected to progress to MDD.^[5,13,14]^ Moreover, MDD is likely to recur once established and often tends to be resistant to treatment.^[15]^ Therefore, intervention for StD is important to prevent the onset of MDD.

Previous studies have confirmed that several interventions are effective against StD.^[16–22]^ However, current reports have shown that medical costs for StD are nearing those for MDD.^[11]^ In addition, individuals with StD are believed to have poor motivation for intensive treatment.^[19]^ Considering the aforementioned limitations, alternative strategies that can easily relieve depressive symptoms among individuals with StD are needed. The SPSRS application we have developed, which is designed to improve depressive symptoms among individuals with StD by presenting positive words through video viewing, can address these issues and shed new light on StD treatment.^[23]^ SPSRS application interventions aim to relive depressive symptoms, thereby preventing progression to MDD and helping users manage their own health. Give that the SPSRS application uses the YouTube Application Programming Interface, users are able to select a favorite video and work on reducing depression symptoms while having fun. Moreover, considering that users need not change their daily routine (e.g., commuting to work), the SPSRS application creates an opportunity for addressing problems related to face-to-face treatment, which ultimately provides substantial benefits to the insurance system and society in general. Hence, we assume that SPSRS applications have great potential as new interventions for individuals with StD given that they reduce the psychological burden of an intervention. Although our previous study showed that SPSRS application interventions improved depressive symptoms among individuals with StD, it only compared outcomes before and after the intervention within a single group without establishing a control group.^[23]^ Therefore, randomized controlled trials (RCTs) based on rigorous methodology are essential to confirm the effectiveness of SPSRS applications for individuals with StD. However, to implement and achieve a high quality RCT, several methodological issues need to be considered and addressed (participant recruitment, administrative problems, harm, etc).^[24,25]^ In fact, reports have shown that several methodological issues have caused one-quarter of RCTs to be discontinued early.^[25]^ One of the best approaches for avoiding failure of a full-scale RCT has been to conduct a pilot RCT.^[26,27]^ Accordingly, a pilot RCT can determine the feasibility a full-scale RCT, increase the likelihood of its success, and prevent failure.^[26]^ Therefore, we herein outline our study protocol for a pilot RCT to investigate the utility of SPSRS application interventions for individuals with StD.

## Objective

2

The present study aimed to determine the feasibility of a future full-scale RCT that will investigate whether SPSRS application interventions could improve depressive symptoms among individuals with StD relative to those receiving no intervention.

### Trial design

2.1

This 5-week, single-blind, 2-arm, parallel-group, randomized, pilot RCT will determine the effectiveness of with the SPSRS application by comparing individuals who had and had not been exposed to the same.

## Methods

3

### Eligibility criteria

3.1

Participants will be selected according to the following eligibility criteria:

Inclusion criteria:

(1)Men and women(2)18 years and older(3)Center for epidemiologic studies depression scale (CES-D) score ≥16.^[28]^(4)Owns a smartphone with an iOS operating system.(5)Written informed consent prior to participation.

Exclusion criteria:

(1)Lifetime history of psychiatric disorders.(2)Currently receiving treatment for a mental health problem from a mental health professional.(3)Vision or hearing deficits that negatively impact everyday life.(4)Experience of a major depressive episode 2 weeks prior to the study ascertained using the Mini-International Neuropsychiatric Interview (MINI).^[29]^

### Interventions

3.2

#### Experimental group

3.2.1

The experimental group included herein will be scheduled to receive video viewing intervention using the SPSRS application designed for iPhones.^[23]^ The SPSRS application is a free video viewing application that uses the YouTube API, which allows individuals to search and watch videos using keywords, similar to a general video playback application. The SPSRS application is programmed to randomly display words that increase confidence, such as “can,” “let us try,” “good luck,” “able,” and “do not worry,” for 17 ms at the 4 corners of the screen.^[6]^ Thereafter, positive words, such as “nice,” “great,” “fantastic,” “satisfactory,” and “enjoyable,” are repeatedly displayed at the center of the screen for 150 ms every 5 seconds.^[30]^ The experimental group will receive a video viewing intervention using the SPSRS application for >10 minutes a day (>70 minutes per week). Given that the intervention period is scheduled for 5 weeks, the experimental group will be receiving > 350 minutes of video viewing intervention using the SPSRS application. Moreover, participants included herein will be able to freely select the videos to watch.

#### Control group

3.2.2

The control group will receive no intervention and no instruction to watch videos using the SPSRS application or other video playback applications during the 5-week intervention period.

#### Criteria for discontinuing or modifying allocated interventions

3.2.3

The intervention or follow-up is discontinued if any of the following occurs:

(1)Participant withdraws consent.(2)The entire clinical trial is discontinued.(3)Non-eligibility is confirmed after registration.(4)The principal investigator or project administrator determines the need for discontinuation.(5)A participant requires treatment for a mental health problem by a mental health professional following hospitalization or the onset of a mental disorder.

The date and reason for discontinuation will be documented in the case report. Participants will also be invited to participate in an outcome-related assessment to determine the effectiveness of the intervention. Participants who refuse to participate in follow-up measurements, provide data, or give consent will be considered withdrawn.

### Strategies for monitoring and improving intervention protocol adherence

3.3

The amount of time participants spend on viewing videos during the intervention will be recorded in the history function of the SPSRS application and will be used for treatment adherence monitoring once a week. Participants who achieve the required video viewing duration per week (i.e., ≥70 minutes) will receive a text message to encourage continued video viewing. However, those who did not meet the required video viewing duration per week will receive a text message informing them regarding the same. In addition, a text message will be sent requesting the participant to make up for the missed viewing time on the subsequent week. Moreover, daily text messages will be sent to encourage the use of the SPSRS application and increase intervention adherence rates.

### Relevant concomitant care and interventions permitted/prohibited during the trial

3.4

From an ethical point of view, no other intervention restrictions will be imposed in this study.

### Outcomes

3.5

The primary outcome will include changes in the CES-D score^[28]^ after the 5-week intervention, while the secondary outcome will include changes in the Kessler Screening Scale for psychological distress (K6)^[31]^ and the generalized anxiety disorder 7-item scale (GAD-7)^[32]^ score following the 5-week intervention.

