### Statistical methods

3.14

Intention-to-treat analysis will be employed herein using data obtained from all assigned participants. A linear mixed models with the restricted maximum likelihood estimation method will then be used to address values missing from the clinical trial, estimate the mean of the primary and secondary outcomes, and compare the experimental and control groups.^[51]^ Group assignment, evaluation time, and interactions between group assignment and evaluation time will be considered fixed effect factors, while participants will be considered random effect factors. The model will use a fixed effect type III test. A 2-sided *P* value of <.05 will be used to indicate statistical significance. No plans for subgroup analysis are currently in place. The latest version of SPSS (SPSS Japan Inc., Tokyo, Japan) will be used for data analysis. In addition, the effect size (Hedge *g*) between the 2 groups and its 95% confidence interval will also be reported.^[52,53]^

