## Discussion

4

StD has been considered an important risk factor for the development of MDD.^[5,13,14]^ Moreover, despite being a precursor to MDD,^[7]^ StD has been associated with poor quality of life,^[1,7,8]^ poor health,^[9]^ impaired daily activities,^[2,10]^ economic costs,^[11]^ mortality,^[12]^ etc. Therefore, interventions aimed at addressing StD are important to prevent the onset of MDD. Incorporating the SPSRS application into interventions is a very innovative method that places less burden on individuals with StD and may improve depressive symptoms. In addition, given the potential for the SPSRS application to influence numerous individuals with StD, it may play an important role in addressing depressive symptoms that may have a significant negative impact on their health. However, RCTs using the SPSRS application for individuals with StD have been lacking. Therefore, a pilot RCT investigating the feasibility of a large-scale trial to determine the effectiveness of the SPSRS application had been planned. The results of this pilot RCT will undoubtedly ensure the successful implementation of a full-scale RCT. In addition, this pilot trial will provide new information through which a higher-quality full-scale RCT can be planned. A particularly important additional information obtained from results of this pilot RCT is that related to the official sample size calculation. Thus, this pilot RCT can provide evidence that reinforces the standard practice of SPSRS application interventions to improve depressive symptoms among individuals with StD.

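### The stated objective is feasibility, but every listed outcome is a symptom scale judged at P<.05, so the objective has no defined answer and 16 per arm cannot carry an efficacy verdict

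*Protocol article*

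**What the plan says.** **Objective (section 2).** "The present study aimed to determine the feasibility of a future full-scale RCT". The abstract's introduction gives the same purpose.

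**Trial design (2.1).** The "pilot RCT will determine the effectiveness of with the SPSRS application". The abstract's methods paragraph says the same.

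**Outcomes (3.5).** "The primary outcome will include changes in the CES-D score" after 5 weeks; "the secondary outcome will include changes in the Kessler Screening Scale for psychological distress (K6") and in GAD-7. Nothing else is listed as an outcome.

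**Statistical methods (3.14).** A REML linear mixed model with group, time and their interaction is applied to primary and secondary outcomes alike. A two-sided P "value of <.05 will be used to indicate statistical significance". Hedges g with its 95% CI is also to be reported.

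**Sample size (3.7).** There are 32 participants, 16 per group, from a rule of thumb of 15 to 20 per group. The between-group difference and SD are declared unknown, and the pilot is to supply them for the full-scale trial.

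**Discussion (4).** The authors expect that "this pilot RCT can provide evidence that reinforces the standard practice of SPSRS application interventions". The limitations paragraph concedes that power may be reduced and asks for care in interpretation.

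**The concern.** A primary outcome should answer the objective. Here the objective asks whether a full-scale trial can be run, and the outcomes ask whether symptoms differ between arms. The introduction justifies the pilot by problems that end trials early (recruitment, administration, harm), yet none of these is an outcome.

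Two things are at stake. First, a report that follows section 3.5 can be complete without saying whether a full-scale trial is feasible. Second, the effectiveness wording and the P<.05 criterion invite readers to take the CES-D test as the result. The sample size was not chosen for that purpose, the control arm receives no intervention, and the outcomes are self-reported by unblinded participants.

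**Working it through.** **1. The plan's own figure.** 2 x 16 = 32, and 16 lies within the cited 15 to 20 per group. The stated size reproduces. The article states no power, effect size or SD, so there is no power figure to check. All effect sizes, correlations and counts below are assumptions.

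**2. Objective against outcomes.**

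| What feasibility needs | Where the article touches it | Listed as an outcome in 3.5? |
|---|---|---|
| Adherence | Viewing time logged and reviewed weekly (3.3) | No |
| Discontinuation | Date and reason documented (3.2.3) | No |
| Retention | Week-5 assessment sought even after discontinuation (3.12) | No |
| Harm | Adverse events monitored and documented (3.16) | No |
| Recruitment | Recruitment window (3.8), central randomisation (3.9) | No |
| Difference and SD for planning | Sample size (3.7), Discussion (4) | Yes, through CES-D |

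One planning quantity is served. The others have data sources but no outcome.

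**3. Power of the P<.05 test at 16 per arm.** Two-sample t test, df = 30, noncentrality d x sqrt(16/2), with d in SDs of the analysed quantity:

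- d = 0.3: 13%
- d = 0.5: 28%
- d = 0.8: 59%
- d = 1.0: 78%
- 80% power requires d of about 1.02.

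By the normal approximation, 80% power would need about 175, 63 and 25 per arm at d = 0.3, 0.5 and 0.8.

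**4. Allowing for baseline.** If CES-D is measured at baseline and week 5 only, with no missing data, the group-by-time test amounts to a t test on change. The SD of change is sqrt(2(1 - r)) score SDs for pre-post correlation r. The article gives no r.

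| r | Power at d = 0.5 | Power at d = 0.8 |
|---|---|---|
| 0.3 | 21% | 46% |
| 0.5 | 28% | 59% |
| 0.7 | 42% | 81% |

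**5. Smallest significant effect.** The critical t on 30 df is 2.042, so the observed d must reach 2.042 x sqrt(2/16) = 0.72. If the true effect were 0.5, a significant result in the favourable direction would overstate it by at least 0.72/0.5 - 1 = 44%. On the change-score scale with r = 0.7, the threshold in score SDs is 0.72 x sqrt(0.6) = 0.56, still above 0.5.

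**6. Precision of the planning quantities.** For an observed g of 0.5, SE = sqrt(2/16 + 0.25/64) = 0.359, so the 95% CI is 0.5 +/- 0.70, or -0.20 to 1.20. A pooled SD on 30 df has a 95% CI of about 0.80 to 1.34 times its estimate.

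**7. Precision of feasibility outcomes** (illustrative counts, exact 95% CIs): 26/32 retained, 64% to 93%; 29/32 retained, 75% to 98%; 12/16 adherent, 48% to 93%.

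**The case against.** The strongest reply is that CES-D belongs in this pilot. Section 3.7 assigns the pilot the task of supplying the difference and SD for the full-scale sample size, and the Discussion calls this particularly important. Those figures can only come from the outcome scale. Section 3.14 already commits to Hedges g with a 95% CI, and the limitations paragraph asks for caution. All of this stands, and it is why CES-D estimation could reasonably remain co-primary.

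Several stronger readings are therefore not supported:

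- A reader might infer that the pilot cannot answer its own question at all. It answers part of it; the rest is undefined.
- A reader might infer that a non-significant P value would end the programme. Section 3.14 ties no progression decision to P<.05, and section 3.22 commits to publication whatever the result.
- A reader might infer that any significant result must be inflated. The true effect is unknown, and a true effect near 1 SD could be detected without serious inflation.
- A reader might fault the missing power calculation or the absence of go/no-go thresholds. The first is not required of a pilot, and the second may sit in the full protocol, which is not shown.

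The power figures also depend on an unstated correlation, as the table shows. What remains is not an omission: the article states a primary outcome and an effectiveness purpose that differ from its stated objective. The call for caution leaves both in place.

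**Conclusion.** The mismatch is in the text and should be corrected. Feasibility is the sole stated objective. All three listed outcomes are symptom scales tested at two-sided P<.05, and the abstract, section 2.1 and the Discussion speak of effectiveness or standard practice. The pilot will produce a rough difference and SD, but no stated outcome addresses recruitment, retention, adherence or harm.

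A P<.05 verdict at 16 per arm is unreliable for small to moderate effects: 13% to 59% power for assumed d of 0.3 to 0.8 with an unadjusted t test, and 46% to 81% at d = 0.8 for assumed correlations of 0.3 to 0.7. The contradiction between objective and outcomes does not depend on those assumptions. The size of the efficacy problem does.

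**What to change.** - **Outcomes (3.5 and abstract).** Name feasibility outcomes as primary, or as co-primary with estimation of the CES-D difference and SD: week-5 questionnaire completion by arm, the share of the experimental arm meeting the weekly 70-minute criterion, discontinuation, and enrolment rate. Give each proportion an exact 95% CI. Sections 3.2.1 (more than 70 minutes) and 3.3 (at least 70) word the criterion differently and must be reconciled before it defines an outcome.
- **Progression criteria.** If any are used, fix them before outcome data are examined. Adherence is reviewed weekly under 3.3, so state what had already been seen when they were set.
- **Symptom scales (3.14).** Report CES-D, K6 and GAD-7 as preliminary between-group estimates with 95% CIs, and draw no effectiveness conclusion from P<.05.
- **Wording.** Replace the statements in the abstract and 2.1 that the trial will determine effectiveness, and remove the standard-practice sentence from the Discussion.

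**Cost.** The adherence, discontinuation and week-5 measures need no new data collection; the enrolment rate needs counts of those screened and randomised. The change needs ethics approval under 3.18 and a registry update. Both should be dated and disclosed, because recruitment was scheduled from October 2019 and the article appeared in January 2020. The feasibility intervals will be wide, so they can support only coarse progression decisions.

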### Participant timeline

3.6

Individuals interested in participating in this study will be assessed for eligibility using interviews and Internet questionnaires. Eligible participants will then be enrolled in the study and randomly assigned to the intervention or control group. The trial period is shown in the consolidated standards of reporting trials diagram^[33]^ (Fig. 1) and Standard Protocol Items: Recommendations for Interventional Trials template^[34]^ (Table 1).

**Figure 1 F1:**
[figure not shown]
CONSORT flowchart of the study design.

**Table 1 T1:**
[figure not shown]
Assessment schedule.

### Sample size

3.7

Four factors are required to calculate the sample size: significance level, power, difference between groups, and standard deviation (SD).^[35]^ However, considering that no previous 2-arm trial has used the SPSRS application for individuals with StD, values for the difference between groups and SD remain unknown. Although a pilot RCT does not require sample size calculations using the aforementioned 4 factors,^[26]^ 15 to 20 participants per group are required to ensure scientific validity of the pilot study results.^[36]^ Therefore, the present study will include a total of 32 participants with 16 participants per group. In addition, the results of this pilot study will provide information on the difference between groups and SD necessary for sample size calculation during the future full-scale study.

### Study setting and recruitment

3.8

Potential participants will be recruited from October 2019 to March 2021 mainly in Okayama Prefecture, Japan through Kibi International University. The research will be promoted widely throughout the Kibi International University Takahashi Campus using advertising flyers. Many facilities will be made available for use by individuals other than students at the Kibi International University Takahashi Campus, while a considerable number participant will be expected given the university's close ties with local communities and surrounding organizations. In addition, the researchers will promote participation using emails and social networking service. All distributed materials will include a dedicated email address through which the research team may be contacted for further information on the study.

